### Engagement, reach and implementation

Measures of engagement with the program include number of text message replies, completed coaching calls, logins to Smartphone applications, and posts on the community blog. These data are collected continuously throughout the nine month trial. Intervention participants are asked to reply ‘OK’ to one text message every three weeks during the intensive phase (weeks 1 to 12) and to each text message sent during the maintenance phase (weeks 14 to 36), while control participants are asked to reply ‘OK’ to all four text messages sent during the intensive phase. Online surveys administered at T1 and T2 follow-up assessments ask participants (intervention and control arms) about their use of, and any problems experienced with, program materials. Socio-demographic data of participants will be used to assess program reach within Medicare Locals. Costs of developing and delivering the program are recorded. The method of recruitment via general practice clinics will also be evaluated for potential as a setting for referring young adults into the program through structured interviews with practice staff involved in the trial.

### Sample size

The average weight loss of young adults participating in an intervention aimed at weight gain prevention is 0.87 kg (95% confidence interval (CI) -1.56, -0.18), while controls gain on average 0.86 kg (95% CI 0.14, 1.57) [19]. To detect a mean difference of 2.0 kg with *P =* 0.05 and 80% power, assuming a standard deviation of 10 kg and a correlation between baseline and final weight of 0.8, 284 subjects are required (142 per arm). Allowing for a 20% drop out, 354 subjects are needed (177 per arm). This number will be sufficient to detect a change in fruit and vegetables of 0.5 serves per day, a 20% change in the proportion having energy-dense take-away meals once a week or less, and an increase in physical activity of 60 minutes per week.

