### Interventions

Control participants receive a mailed two-page handout summarizing the Australian national dietary and physical activity guidelines [24,25], an introductory call (week 0) to introduce the program (no coaching given), four SMS text messages (one every three weeks during weeks 1 to 12) that re-iterate information in the handout, and limited access to the TXT2BFiT website, that is, electronic versions of the two-page handout, consent form and study information statement, general information about the study and contact information. Intervention participants are mailed an eighteen-page booklet containing the two-page control handout, as well as sample meal plans, recommendations for daily servings from the core food groups with example serving sizes [25], and information about the four target behaviors addressed by the program: physical activity and sedentary behavior, intake of fruit and vegetables, intake of energy-dense take-away meals, and SSB intake, in conjunction with the TXT2BFiT mobile phone-based program.

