#### TXT2BFiT program

This tailored program consists of SMS text messages, Emails, Smartphone mobile applications, a study website and personalized coaching calls (Figure 1). The program is grounded on processes-of-change theory [26], supported by self-monitoring, motivational interviewing and goal setting [27,28]. Through its various intervention components, the TXT2BFiT program consistently encourages participants to (1) consume five servings of vegetables and two servings of fruit per day, in line with the national dietary recommendations [25]; (2) limit energy-dense take-away meals to once per week or less [15]; (3) limit SSB to less than one liter per week [14]; (4) perform 60 minutes or more of moderate-intensity physical activity most days of the week (preferably daily), as evidence indicates that young adults are likely to require physical activity levels exceeding national guidelines to a level of approximately 45 to 60 minutes per day or 1.7 PAL (physical activity level; ratio of total to basal energy expenditure) to prevent weight gain [12,29].

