#### Secondary outcomes

Frequency of consuming specific foods and drinks (fruit, vegetables, energy-dense take-away meals, SSB, and water) is assessed using short dietary questions [43,44]. Knowledge of fruit and vegetable recommendations is assessed using the question ‘What do you think is the recommended number of serves of (fruit/vegetables) that should be eaten in a day?’ adapted from Pollard *et al*. [45]. Multiple choice response options are ‘one serve a day’, ‘two or three serves a day’, ‘four or five serves a day’ and ‘six or more serves a day’ for fruit and ‘one or two serves a day’, ‘three or four serves a day’ and ‘five or more serves a day’ for vegetables. Intake of specific nutrients (energy, protein, total fat, saturated fat, carbohydrate, sugars, dietary fiber, and alcohol) is assessed using an online food frequency questionnaire, the Dietary Questionnaire for Epidemiological Studies version 2 (DQES v2), administered at baseline and three months [46]. Stage-of-change for the target dietary behaviors (fruit, vegetables, energy-dense take-away meals and SSB) is assessed by firstly measuring the target behavior, for example, serves of vegetables eaten per day. Participants reporting the desired behavior (that is, vegetable serves five or more per day; fruit serves two or three per day; energy-dense take-away meals ≤ once per week; SSB < 1 L per week) are directed to the question: ‘Have you been eating/drinking this amount of (behavior) for more than six months?’ to classify them as being in either action (performing the desired behavior for ≤ six months) or maintenance (performing the desired behavior for > six months). Participants not performing the desired behavior are asked: ‘Are you thinking about eating/drinking more/less (behavior) sometime in the next six months?’ to classify those in contemplation/preparation (intent on changing in ≤ six months) or pre-contemplation (not intent on changing in ≤ six months). Participants intent on changing in ≤ six months are further asked: ‘Are you planning to eat/drink more/less (behavior) sometime in the next month?’ to discriminate between those in preparation (intent on changing in ≤ one month) or contemplation (not intent on changing in ≤ one month).

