### Statistical analysis

The primary outcome, body weight at three months, will be compared between the two groups using analysis of covariance adjusting for baseline weight and the stratification variables Medicare Local, general practice clinic and participant gender. The analysis will be by ‘intention-to-treat’ principle using multiple imputation to account for missing data. Secondary outcomes that are continuous will also be analyzed using analysis of covariance, while Chi-squared tests will be used to analyze dichotomous outcomes. Mixed models will be used to describe changes in outcomes over time. Personnel analyzing participant outcomes will be blinded to participant allocation. Further sensitivity analyses will be conducted using measures of participant engagement with program materials.

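### Take-away meal frequency is collected but expressed only as the proportion at once a week or less, which implies a yes/no comparison that drops grading and baseline (optional improvement, secondary outcome)

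*Protocol article*

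**What the plan says.** Under Outcome measures, Secondary outcomes, the article states: "Frequency of consuming specific foods and drinks (fruit, vegetables, energy-dense take-away meals, SSB, and water) is assessed using short dietary questions". It does not list the response options for take-away meals.

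Sample size, after deriving 142 per arm (284) from body weight, says the number also suffices for "a 20% change in the proportion having energy-dense take-away meals once a week or less". In the same sentence, fruit and vegetables are given in serves per day and physical activity in minutes per week.

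Statistical analysis names two between-arm methods for secondary outcomes: "Secondary outcomes that are continuous will also be analyzed using analysis of covariance", and "Chi-squared tests will be used to analyze dichotomous outcomes". No ordinal or count method is named. It adds: "Mixed models will be used to describe changes in outcomes over time".

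The cut is the program's own goal. The TXT2BFiT program section encourages participants to "limit energy-dense take-away meals to once per week or less", and the stage-of-change algorithm treats "energy-dense take-away meals ≤ once per week" as the desired behavior. The same threshold, in the other direction, is one of the alternative eligibility conditions in Table 1.

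**The concern.** A frequency carries more information than whether it falls on one side of a cut. On a yes/no scale, a participant who goes from five take-away meals a week to two counts as unchanged, while one who goes from two to one counts as a full success. The comparison cannot see reductions that stay above the cut.

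A plain Chi-squared test also makes no use of baseline frequency. Table 1 joins the eligibility behaviors by and/or, so some participants can enter already at once a week or less. They cannot improve on the binary outcome, and an unadjusted test does not separate them from the rest.

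Take-away intake is one of the target behaviors (the Interventions section refers to "information about the four target behaviors addressed by the program"), and better diet is part of the stated hypothesis. What is at stake is power and sensitivity for one secondary outcome. The body weight analysis is unaffected.

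**Working it through.** **1. The plan's own figure.** Inputs from Sample size: difference 2.0 kg, SD 10 kg, correlation 0.8, P = 0.05 (taken as two-sided), 80% power. Residual SD = 10 × √(1 − 0.8²) = 6. Per arm: 2 × (1.960 + 0.842)² × 6² / 2² = 141.3, so 142 per arm and 284 in all, as stated. Dividing by 0.8 gives 355 against the stated 354, a rounding difference.

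**2. Power of the binary test with 142 per arm.** The control proportion is not given, so it is varied.
- 20% as percentage points: 93.5% power for 30% vs 50%, 92.5% for 40% vs 60% (the lowest), 93.5% for 50% vs 70%. The article's sufficiency statement holds on this reading.
- 20% as a relative change: about 8% power at a control proportion of 10%, 39.5% at 50% (50% vs 60%), 57% at 60%, 80% at 70%. On this reading the statement fails over most of the range.

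**3. Information lost by the cut.** Under proportional odds with 1:1 allocation, information on the log odds ratio is proportional to 1 − Σp³, where p are the category proportions averaged over arms. For a cut with proportion q on one side this is 1 − q³ − (1 − q)³. For a very fine scale it tends to 1. The category proportions below are assumptions.

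| Scale and split | Graded | Binary | Loss |
|---|---|---|---|
| 3 categories 15/35/50%, cut at 50% | 0.829 | 0.750 | 10% |
| 5 categories 10/40/30/15/5%, cut at 50% | 0.905 | 0.750 | 17% |
| 5 categories 10/30/35/20/5%, cut at 40% | 0.921 | 0.720 | 22% |
| Fine scale, 50:50 | 1 | 0.750 | 25% |
| Fine scale, 40:60 | 1 | 0.720 | 28% |
| 5 equal categories, 20:80 | 0.960 | 0.480 | 50% |
| Fine scale, 20:80 | 1 | 0.480 | 52% |

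More extreme splits lose more (73% for a fine scale at 10:90).

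**4. What that means for power.** Information V = (284/12) × (1 − Σp³); power = Φ(log OR × √V − 1.96).
- 40% vs 60%: OR = (0.6/0.4)/(0.4/0.6) = 2.25, log OR 0.811. Binary: V = 23.67 × 0.75 = 17.75, power 93%. Five equal categories: V = 22.72, power 97%. Fine scale: V = 23.67, power 98%. The gain is about 4-5 points. For 80% power the requirement is about 96 per arm binary against 72-75 graded.
- 50% vs 60%: OR 1.5, log OR 0.405. Binary: V = 23.67 × 0.7425 = 17.57, power 40%. Five equal categories: 49%. Fine scale: 50-51%. The gain is about 9-11 points. Simulation under a latent shift on 4-5 categories, or with Poisson or negative binomial weekly counts, gives 48-54% against 38-40%, a gain of about 10-14 points.

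These figures concern the outcome scale only. Any gain from baseline adjustment comes on top and cannot be sized, because no baseline correlation is given for take-away meals.

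**The case against.** The strongest reply has four parts.

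*The yes/no test is inferred.* Statistical analysis never assigns take-away meals to the dichotomous class, Sample size states what the number can detect and does not prescribe an analysis, and the mixed models are on an unstated scale. This stands. A reader might infer that the article rules out a graded analysis; it does not. What remains is that the only scale given for this outcome is a proportion, and the only test named for a proportion is Chi-squared.

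*The cut is meaningful.* It is the program target, an eligibility threshold and the stage-of-change threshold. The proportion meeting it is a legitimate, interpretable result and should be kept. That is a reason to report it, but not to discard the rest of the scale.

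*The consequence is small.* On the percentage-point reading the binary test is already well powered. On the relative reading, at 50% vs 60%, both tests are underpowered, and the main problem is the unclear meaning of the 20%. Both points stand.

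*The gain depends on the model.* The calculations assume a common shift along the scale. If the effect is concentrated at the coached threshold, the advantage of a graded test shrinks. This also stands.

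**Conclusion.** The point holds as an optional improvement to one secondary outcome. Taken together, the sections imply a comparison that leaves collected information unused: the grading of the response and the baseline frequency.

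A reader might put a single figure on the loss, such as a quarter. The document does not support one. A quarter is right for a fine scale cut near the median under proportional odds. Without the response categories and the expected split, the defensible statement is a range: about 10-22% for coarse, uneven scales cut near the middle, 25-28% for a fine scale near the median, about 50% at 20:80. The power gain is about 4-5 points near the ceiling for 40% vs 60%, and about 10-14 points for an assumed 50% vs 60%.

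A reader might also extend the criticism to stage-of-change and self-efficacy. Nothing in the article says that these are dichotomized, so the point does not cover them.

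**What to change.** In Statistical analysis, state that take-away meal frequency is compared between arms on its recorded scale, with a proportional-odds model if the responses are ordered categories or a negative binomial model if they are weekly counts. Adjust for baseline frequency and the stratification factors. Report the proportion at once a week or less in each arm beside it, as the readable summary of the program target.

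In Sample size, keep the 20% figure for that proportion, and say whether it is absolute or relative.

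The cost is two or three sentences and a standard model, with no new data, visits or participants. The downside is that an odds or rate ratio is less immediate than a percentage meeting the target, which is why the percentage stays in the report.

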### Randomization

Eligible patients are randomized in a 1:1 ratio into intervention and control arms. Randomization is based on a stratified randomized block design, where the strata are the Medicare Local, general practice clinic, and participant gender. The random sequence will be generated by an independent researcher and concealed from those responsible for enrolling and assigning interventions to patients.

### Statistical analysis

The primary outcome, body weight at three months, will be compared between the two groups using analysis of covariance adjusting for baseline weight and the stratification variables Medicare Local, general practice clinic and participant gender. The analysis will be by ‘intention-to-treat’ principle using multiple imputation to account for missing data. Secondary outcomes that are continuous will also be analyzed using analysis of covariance, while Chi-squared tests will be used to analyze dichotomous outcomes. Mixed models will be used to describe changes in outcomes over time. Personnel analyzing participant outcomes will be blinded to participant allocation. Further sensitivity analyses will be conducted using measures of participant engagement with program materials.

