**Inclusion criteria**	
1	Body mass index 25.0 to 31.9 kg/m^2 ^or 23.0 to 24.9 kg/m^2^ with reported weight gain > 2 kg over past 12 months.
2	Aged 18 to 35 years.
3	Fruit intake < two serves/day and/or vegetable intake < five serves/day and/or sugar sweetened beverage intake ≥ 1 L/week and/or energy-dense take-away meals > once/week and/or moderate intensity physical activity < 60 minutes/day.
4	Has mobile phone capable of receiving text messages and access to the Internet at least once a week.

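### Dichotomous secondary outcomes get an unadjusted chi-squared test although their baseline value is collected; the test is valid, but adjusting for baseline would add power at almost no cost

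*Protocol article*

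**What the plan says.** The Statistical analysis section treats three kinds of outcome differently.

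- Primary outcome: "analysis of covariance adjusting for baseline weight and the stratification variables Medicare Local, general practice clinic and participant gender".
- Continuous secondary outcomes: "Secondary outcomes that are continuous will also be analyzed using analysis of covariance". Covariates are not listed again, but the natural reading is adjustment for the baseline value.
- Dichotomous outcomes: "Chi-squared tests will be used to analyze dichotomous outcomes". No covariate is named.

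Mixed models also appear, but in a descriptive role: "Mixed models will be used to describe changes in outcomes over time". They are not named as the between-arm test for dichotomous outcomes.

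The Sample size section gives one dichotomous target, "a 20% change in the proportion having energy-dense take-away meals once a week or less". It states neither a control proportion nor whether the change is absolute or relative. Under Outcome measures, the same online survey is completed at baseline, three months and nine months, so baseline status on each behaviour is known. Table 1 joins the entry behaviours by and/or ("energy-dense take-away meals > once/week and/or moderate intensity physical activity < 60 minutes/day"), so a participant can qualify on one behaviour while already meeting the target on another.

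**The concern.** Where participants differ in baseline status, and that status predicts follow-up status, an unadjusted comparison carries variation that could have been removed. The plan uses this principle for body weight, where it sets the sample size, and then drops it for the dichotomous behaviours. At stake is the chance of detecting moderate changes in secondary outcomes that the intervention targets directly. Because the article names the test, an analysis plan that follows it would inherit the loss.

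**Working it through.** **1. The plan's own figure.** Inputs from Sample size: difference 2.0 kg, SD 10 kg, correlation 0.8, 80% power, alpha 0.05 (taken as two-sided).

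n per arm = 2(1.96 + 0.8416)² × SD²(1 − r²) / difference² = 2 × 7.849 × 36 / 4 = 141.3, so 142 per arm and 284 in total, as stated. Without baseline adjustment, 2 × 7.849 × 100 / 4 = 392.4, so 393 per arm. Dropout: 284 / 0.8 = 355 against the stated 354, a rounding difference. The sample size therefore relies on baseline adjustment.

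**2. Chi-squared power at 142 per arm** (normal approximation, two-sided 0.05).

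- 20 points absolute: 0.925 at 40% v 60%, the least favourable pair tried, rising to 0.99 at 10% v 30%.
- 15 points: 0.72 to 0.77 for control proportions of 30% to 60%.
- 10 points: 0.40 to 0.42 over the same range.

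**3. Expected gain from the baseline value.** If phi is the correlation between baseline and follow-up status, adjustment multiplies the variance by about 1 − phi². This is 0.91, 0.75 and 0.64 at phi 0.3, 0.5 and 0.6, equivalent to 9%, 25% and 36% of the sample size. For 15 points centred on 50%, power moves from 0.717 to 0.757, 0.834 and 0.888.

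**4. Simulation A.** 142 per arm, 50% baseline prevalence, latent bivariate normal, treatment shift 0.35 SD (about 50% v 64% at follow-up), 1,500 trials per setting. At 50% prevalence a latent correlation r corresponds to phi = (2/π) arcsin(r).

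| Latent r | phi | Chi-squared | Logistic + baseline |
|---|---|---|---|
| 0.5 | 0.33 | 0.655 | 0.708 |
| 0.7 | 0.49 | 0.625 | 0.732 |
| 0.85 | 0.65 | 0.647 | 0.853 |

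Type I error was 0.045-0.051 for chi-squared and 0.047-0.052 for the adjusted model.

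**5. Simulation B.** N = 284, control proportion about 45%, 10 clinics, blocks of four within clinic and gender, 2,000 trials per setting.

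| phi | Difference | Chi-squared | Logistic + baseline | Also gender and clinic (fixed) |
|---|---|---|---|---|
| 0.3 | 10 | 0.402 | 0.426 | 0.442 |
| 0.3 | 15 | 0.722 | 0.768 | 0.776 |
| 0.3 | 20 | 0.926 | 0.946 | 0.952 |
| 0.5 | 10 | 0.402 | 0.490 | 0.505 |
| 0.5 | 15 | 0.726 | 0.838 | 0.850 |
| 0.5 | 20 | 0.940 | 0.987 | 0.990 |
| 0.6 | 10 | 0.401 | 0.549 | 0.564 |
| 0.6 | 15 | 0.726 | 0.896 | 0.905 |
| 0.6 | 20 | 0.936 | 0.992 | 0.994 |

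Chi-squared type I error was 0.044-0.054. The Monte Carlo standard error at a power near 0.73 is √(0.73 × 0.27 / 2000), about 0.01.

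**6. Strata alone.** At 15 points, Mantel-Haenszel over clinic and gender gave 0.726 against 0.722 for chi-squared (phi 0.3), and 0.728 against 0.726 (phi 0.5).

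**7. Many small clinics.** With 30 clinics, a wider clinic spread and 1,200 trials, fixed clinic effects gave a type I error of 0.075, against 0.052 for chi-squared and 0.058 for logistic with baseline only. The standard error at 5% is √(0.05 × 0.95 / 1200) = 0.006, so 0.075 is not noise.

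**The case against.** The strongest reply is that nothing here is wrong. With "Eligible patients are randomized in a 1:1 ratio into intervention and control arms", a chi-squared test compares the arms validly, and chance imbalance at baseline does not bias a randomized test. These are secondary outcomes, the correlations are assumed, and high stability cannot be presumed in a trial meant to change behaviour. All of that stands. It limits the point to efficiency and makes the size uncertain, but the gain was positive in every setting with a real effect.

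A reader might infer more than the article supports:

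- That the sample-size statement on take-away meals fails. For an absolute change of 20 points it does not. On a relative reading, chi-squared power would be 0.27 (40% to 48%), 0.40 (50% to 60%), 0.57 (60% to 72%) or 0.80 (70% to 84%), but the article gives neither the reading nor a control proportion.
- That ignoring the strata costs power, since "the strata are the Medicare Local, general practice clinic, and participant gender". In simulation B it cost almost nothing, and type I error stayed near nominal.
- That stage-of-change and self-efficacy will be dichotomised and need an ordinal model. The article defines their categories but never says they will be collapsed.
- That missing confidence intervals or pooling rules for imputed data are defects. A condensed article may leave these to the analysis plan.

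The mixed models soften the point without removing it, because they are described as descriptive.

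**Conclusion.** The point holds as an efficiency improvement to valid secondary tests. At 142 per arm and a difference of 14 to 15 points, baseline adjustment adds about 5 to 21 percentage points of power (from 63-73% to 71-90%). At 20 points absolute it adds about 2 to 6. These figures assume control proportions near 45-50% and a baseline/follow-up phi of about 0.3 to 0.65; the article gives neither. Almost all of the gain comes from the baseline value: gender and clinic together added at most 1.6 points with 10 clinics. It would go too far to call the chi-squared test biased, or to call every form of adjustment free, since fixed effects for many small clinics inflated type I error.

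**What to change.** Replace the chi-squared test with logistic regression of follow-up status on arm, baseline status of the same outcome and gender. Handle clinic parsimoniously, for example by a random intercept, and not by fixed effects for many small clinics. The random intercept was not itself simulated, so its behaviour at the expected number of clinics is worth a short check. Gender and clinic are kept for consistency with the primary analysis and the randomization, not for power.

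Report the treatment effect as an odds ratio and a standardized risk difference, each with a 95% confidence interval. The risk difference can be set directly against a target stated as a change in a proportion. Both estimates, the odds ratio on the log scale, can be pooled across the imputed datasets.

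The cost is one sentence of the plan, changed before outcomes are compared by arm. Every covariate is already collected, and no visit or participant is added.
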